#### Aim 2: implementation science

Implementation outcomes: A recent systematic review of implementation outcome measures informed our selection process [49]. We identified four measures [46] (see Additional file 1: Table S1). The first three implementation outcomes will be measured in the early phase of implementation, while the remaining one will be measured following delivery of the intervention.

Barriers and facilitators: We will explore the factors associated with implementation effectiveness as described in the Consolidated Framework for Implementation Research [47]. Their identification will further inform the interpretation of clinical outcomes and implementation planning for future scale up.

### Statistical analysis

The primary outcome is the IBD-DI ordinal measure at the end of the treatment period (1–2 years after transfer). We will compare groups using the Wilcoxon-Mann–Whitney test, and statistical significance set at P < 0.05.

Secondary outcome measures will be analyzed at study completion and interim time points by comparing participants in the intervention and control arms using Wilcoxon-Mann–Whitney test. In addition, repeated measures analysis will determine changes over time for the primary and secondary outcome measures at three timepoints (baseline, time of transfer, end of study).

Assessment of health services outcomes will be conducted by linking clinical to health administrative data. Likelihood of emergency department use and hospitalization after transfer will be compared using multivariable logistic regression analysis. Number of ED and outpatient visits will be determined using either Poisson regression or negative binomial regression. All models will include confounders reported in Canadian health services studies of IBD patients: age at diagnosis, age at transfer, sex, rural/urban household, and socioeconomic status.

Assessment of implementation outcomes will be determined using mixed methods (quantitative and qualitative) assessment, as described above.

Sample size calculation: The IBD-DI ranges in score from 0–100. The categories of disability are 0–20 (no disability), 20–35 (mild disability), 35–50 (moderate disability), and 50–100 (severe disability). In the original validation study of the IBD-DI, the mean score of patients was 35.3 ± 20.5. We would consider the goal of this transition program to allow AYAs to achieve a mean level of < 20 (no disability), presenting a 16-point decrease from the mean baseline, or a Cohen effect size (*d*) of 0.78.

Assuming alpha-probability of 0.05, 46 patients would be required to achieve a power of 80% (23 in each group), and 62 patients would be required to achieve a power of 90% (31 in each group) (calculated using G*Power version 3.1.9.7). Assuming a drop-out rate of 25% in each group over the course of the study, we will aim to enroll 90 participants (45 in each group). This calculation is likely an underestimation of the study’s power. Two simulation studies have demonstrated that stratified randomization increases study power in trials with sample sizes < 100 [48, 49]. There is no established method for sample size calculation that accounts for stratified randomization [50]. We will limit enrollment to 40 participants from SickKids, and 25 from other sites in order to ensure distributed enrollment across sites and reduce the risk of health system bias.

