### Randomization, concealment of allocation, and blinding

A subgroup of treating healthcare providers (physicians and nurses) will solicit interest in the study during their clinic appointments and based on clinic lists of their eligible patients compiled by research staff. The program is not being trialed with all IBD clinicians at all sites; this is appropriate for a Hybrid 1 design. Willing participants will then be consented by research staff who will also randomize them at enrollment (1:1) by research staff using two strata: center of care and IBD-DI severity (no/mild disability (scores of 0–34) vs. moderate/severe disability (scores of 35–100)) to ensure balance between the intervention and control arms in those strata. Randomization will occur directly in the REDCap (Vanderbilt University, Nashville, TN) database using the randomization function [23] and allocation will be concealed. Blinding is not possible as the transition navigators need to interact directly with the participants and their treating healthcare teams.

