### Outcome measures

See Table 5 for summary of primary and secondary outcome measures.

**Table 5 Tab5:** Primary and Secondary Outcome Measures. Note: Primary and secondary outcomes will be measured at enrollment (T1), at the time of transfer to adult care (T2), and at the end of the study period (1–2 years after transfer) (T3), unless otherwise specified

Domain	Measure	Timing of administration
*Primary outcome*		
Disability and function	IBD-DI [26, 27]	T1, T2, T3
*Secondary outcomes*		
Transition readiness	Transition Readiness Assessment Questionnaire (TRAQ) [28] Transition Success Scores (TSS)	T1, T2, T3
Bio-psychosocial risk	Pediatric IBD INTERMED [24]	T1, T2, T3
Disease-related knowledge	IBD-KID2[29]	T1, T2, T3
Quality of life	IBDQ-32[57]	T1, T2, T3
Self-efficacy	IBD Self-Efficacy Scale—Adolescent (IBD-SES-A) [58]	T1, T2, T3
Mental Health	Patient Health Questionnaire-9 (PHQ-9) Generalized Anxiety Disorder-7 (GAD-7)	T1, T2, T3
Disease activity	Physician global assessment (PGA) of disease activity Modified Harvey Bradshaw Index (HBI) Assessment for CD Activity [44] Pediatric Ulcerative Colitis Activity Index (PUCAI) for UC Activity [45] Fecal calprotectin *(at enrollment and study termination only)*	T1, T2, T3 T1, T3
Health services utilization	Emergency department visit after 18th birthday (yes/no) Number of emergency department visits after 18th birthday Hospitalization after 18th birthday (yes/no) Number of outpatient visits to GI after 18th birthday	T3

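### The primary Wilcoxon-Mann–Whitney test uses neither baseline IBD-DI nor center, so it loses power to the extent that baseline predicts the outcome

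*Protocol article*

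**What the plan says.** All references are to the protocol article.

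- **Primary endpoint and test (Statistical analysis).** "The primary outcome is the IBD-DI ordinal measure at the end of the treatment period (1–2 years after transfer"). The comparison is then fixed: "We will compare groups using the Wilcoxon-Mann–Whitney test, and statistical significance set at P < 0.05". No covariate or stratum is named.
- **Randomization (Randomization, concealment of allocation, and blinding).** Staff "randomize them at enrollment (1:1) by research staff using two strata: center of care and IBD-DI severity", with severity split at scores of 0–34 versus 35–100.
- **Baseline measurement (Outcome measures, Table 5).** "Primary and secondary outcomes will be measured at enrollment (T1"), and IBD-DI is listed at T1, T2 and T3.
- **Other analyses (Statistical analysis).** A repeated measures analysis over baseline, transfer and end of study is added for the primary and secondary measures. Secondary scales are also compared by Wilcoxon-Mann–Whitney (WMW). The only covariate list follows the health-services models, and it contains neither center nor baseline IBD-DI.
- **Power (Statistical analysis, sample size calculation).** The goal is to "achieve a mean level of < 20 (no disability), presenting a 16-point decrease from the mean baseline". The stated power is said to be an underestimate because "Two simulation studies have demonstrated that stratified randomization increases study power in trials with sample sizes < 100".

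**The concern.** Stratified randomization makes the arms more alike on the stratifying factors. If those factors predict the outcome, the true sampling variance of the arm difference shrinks. A two-group rank test still takes its null variance from the pooled scores, as if allocation had been unrestricted. It then rejects too rarely under the null and fails to turn the better balance into power. Continuous baseline IBD-DI carries more information than its two-level version, and that is also unused.

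Efficiency is at stake, not validity. The sample is small (90 enrolled, about 67 evaluable), and the plan counts stratification as a reserve of power that its own primary test largely cannot draw on. The loss would be felt most if the true difference is below 16 points. That is realistic, because controls also receive assessments, checklists, webinars and a transfer letter, and the Limitations section concedes that they may do better through monitoring.

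**Working it through.** **Inputs from the protocol article.** Mean and SD come from "the mean score of patients was 35.3 ± 20.5". The effect is 16 points (16/20.5 = 0.78). Planned sizes are 23 and 31 per group for 80% and 90% power. Enrollment is 90 with 25% drop-out, so 90 × 0.75 = 67.5 evaluable, or about 33 per arm.

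**Assumptions, not in the documents.** The baseline-to-outcome correlation ρ is taken as 0, 0.3, 0.5 and 0.7. Scores are normal, blocks have size 4, the four centers enroll 36/18/18/18 (within the stated caps of 40 and 25), drop-out is random, and tests are two-sided at 0.05. The severity cut of 35 is treated as the mean, since the assumed mean is 35.3.

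**Step 1: the plan's own figures.** I used noncentral-t power with n multiplied by 3/π, the efficiency of the WMW test under normality. With one-sided alpha 0.05 this gives exactly 23 and 31 per group. Two-sided it gives 29 and 38 (58 and 76 in total). The sample size is therefore consistent with the unadjusted rank test; sidedness is a separate question. At 33 per arm, two-sided WMW power for d = 0.78 is 0.86.

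**Step 2: why the test becomes conservative.** Splitting a normal baseline at its mean keeps 2/π = 0.637 of its variance, so the severity stratum explains f = 0.637ρ² of the outcome variance. With perfect balance, the standard error of the arm difference is √(1 − f) of what an unadjusted test assumes. The effective critical value is then about 1.96/√(1 − f):

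| ρ | f | √(1 − f) | Effective cut-off | Limiting type I error |
|---|---|---|---|---|
| 0 | 0 | 1 | 1.96 | 0.050 |
| 0.3 | 0.057 | 0.971 | 2.02 | 0.044 |
| 0.5 | 0.159 | 0.917 | 2.14 | 0.033 |
| 0.7 | 0.312 | 0.829 | 2.36 | 0.018 |

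These are limits. Unfilled blocks and drop-out weaken the balance, so actual values should lie between them and 0.05.

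**Step 3: simulation of the whole design.** Each ρ used 4,000 runs under the null and 2,000 per power value, with no center effect. ANCOVA is on baseline IBD-DI and center.

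| ρ | WMW type I | Power at 16 points: WMW / ANCOVA | Power at 10 points: WMW / ANCOVA |
|---|---|---|---|
| 0 | 0.046 | 0.87 / 0.88 | 0.48 / 0.50 |
| 0.3 | 0.049 | 0.86 / 0.89 | 0.48 / 0.53 |
| 0.5 | 0.038 | 0.89 / 0.95 | 0.48 / 0.61 |
| 0.7 | 0.025 | 0.89 / 0.99 | 0.47 / 0.77 |

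ANCOVA type I error stayed at 0.047–0.053. The Monte Carlo standard error is √(0.05 × 0.95/4000) = 0.003 for the null column and at most about 0.011 for power. A repeat with another seed gave WMW type I errors of 0.051, 0.044, 0.036 and 0.024, and power at 16 points of 0.86, 0.87, 0.88 and 0.89 against 0.87, 0.91, 0.95 and 0.99. A center effect with SD 0.3 of the outcome SD gave the same pattern.

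**Step 4: formula check on ANCOVA power.** Power ≈ Φ(0.78 × √(33/2)/√(1 − ρ²) − 1.96). Since 0.78 × √16.5 = 3.168, this gives Φ(1.36) = 0.91, Φ(1.70) = 0.96 and Φ(2.48) = 0.99 for ρ = 0.3, 0.5 and 0.7. These agree with the simulation.

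**Step 5: what stratification buys the planned test.** As ρ rises from 0 to 0.7, WMW power moves from 0.866 to 0.893 at 16 points (about 3 percentage points) and from 0.476 to 0.473 at 10 points (none).

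**Step 6: choice of remedy.** Over the same four correlations, a stratified rank test (van Elteren) on the eight strata has power of 0.81, 0.83, 0.88 and 0.93 at 16 points. That is below the unadjusted test at ρ of 0.3 or less. Rank-ANCOVA on continuous baseline and center gives 0.86, 0.87, 0.93 and 0.99.

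**The case against.** The strongest defense is that this is a valid test. It introduces no bias and no excess of false positives, it suits an outcome that the protocol calls ordinal, and it matches the way the trial appears to have been sized. At the planned 16-point effect its two-sided power is about 0.86–0.89 whatever the correlation. All of that stands, and it limits the point to efficiency.

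The correlation is also unknown. The interval is long (one section puts the outcome at 3 years after enrollment), it spans transfer of care, and the intervention is meant to change the score. A low correlation cannot be excluded; at 0 to 0.3 the loss is small and type I error close to nominal. A reader might infer that the test is conservative in any event. The documents do not support that; it depends on ρ. Some positive correlation is nevertheless plausible, because the same instrument is used in the same patients and its baseline was chosen as a stratifier.

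Two further inferences go too far. One is that baseline is ignored altogether: the repeated measures analysis uses it for primary and secondary measures, although as an addition to the named primary test. The other is that the result could not be read against the 16-point target. Naming a rank test does not preclude reporting means or a shift estimate, and such reporting is commonly left to the analysis plan.

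Finally, the statement that stratification raises power is qualitative and rests on studies not available here. It is not false at the planned effect, where the gain is about 3 percentage points.

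**Conclusion.** The point holds as a conditional efficiency concern about a choice that the protocol article fixes explicitly. Against ANCOVA on baseline and center, the unadjusted test loses about 1, 3–4, 6–7 and 10 percentage points of power at a 16-point difference for correlations of 0, 0.3, 0.5 and 0.7. At a 10-point difference it loses about 2, 5, 13–14 and 30. Its type I error is about 0.05, 0.045–0.05, 0.04 and 0.025. Most of the power gain attributed to stratification is not realized by this test.

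The sizes rest on the assumed correlations, normal scores, blocks of 4, random drop-out and two-sided testing. The direction is secure; the magnitude is not known from the documents. The change should be made, but the trial is not invalid without it.

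**What to change.** - **Primary analysis.** Regress T3 IBD-DI on arm, with baseline IBD-DI as a continuous covariate and center as a factor. Linear ANCOVA, rank-ANCOVA, or a cumulative-odds model if the score is kept ordinal would all serve; name one in advance. Report the adjusted effect with its 95% CI.
- **Sensitivity analysis.** Keep the WMW test. Do not rely on a rank test stratified over eight small cells as the remedy.
- **Secondary scales.** Adjust each for its own T1 value.
- **Sample size text.** State that most of the power gain from stratification depends on the adjusted analysis.

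The cost is wording in the analysis plan. Baseline IBD-DI and center are already recorded, and recruitment had not started when the article was submitted. The change should be fixed before any comparison of outcomes by arm.

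### Five mandatory covariates plus arm leave at most 7.5 events per parameter in the logistic models for emergency visits and hospitalization; a penalized fit is a cheap safeguard

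*Protocol article*

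**What the plan says.** The health services paragraph of the Statistical analysis section states: "Likelihood of emergency department use and hospitalization after transfer will be compared using multivariable logistic regression analysis". It then fixes the adjustment set: "All models will include confounders reported in Canadian health services studies of IBD patients: age at diagnosis, age at transfer, sex", and completes the list with rural or urban residence and socioeconomic status. The set is mandatory for every model in that paragraph. No penalized or exact fit is mentioned, so ordinary maximum likelihood is the natural reading.

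The sample size text, which concerns only the IBD-DI, says "we will aim to enroll 90 participants (45 in each group", and before that: "Assuming a drop-out rate of 25% in each group over the course of the study". Table 5 lists the two binary outcomes (any emergency visit, any hospitalization) as secondary. The Outcome measures section obtains utilization by linkage to provincial administrative data. No event rate is given for either outcome, and no coding for socioeconomic status.

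**The concern.** Maximum-likelihood logistic regression is unreliable when the rarer outcome category is small relative to the number of fitted parameters. Non-null log odds ratios then tend to be pushed away from zero, and a covariate pattern can predict the outcome perfectly, so that no finite estimate exists. Here the covariate list is fixed while the sample was sized for a different, continuous-type outcome. These models are meant to show whether the programme changes use of health services. An exaggerated odds ratio, or a model that has to be altered after the data are seen, would weaken that evidence. Because the covariate set is stated as a rule, this is a choice the protocol has made and not a detail left for later.

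**Working it through.** **Inputs.** Enrolment is 90 at 1:1, and drop-out is 25%, so 90 × 0.75 = 67.5, about 68 (both from the sample size text). Five covariates come from the Statistical analysis section. With arm that is 6 parameters, or 9 if socioeconomic status enters as quintiles (1 + 4 + 4; the coding is an assumption).

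**The plan's own figures.** None exists for the logistic models. The effect size for the IBD-DI reproduces: 16/20.5 = 0.78. The stated 23 and 31 per arm reproduce for a Wilcoxon test at one-sided 0.05; a two-sided test gives 29 and 38. The sidedness is not stated, and that is a separate matter. Drop-out: 62/0.75 = 82.7, so 83, which the plan takes up to 90. Nothing in this calculation refers to emergency visits or hospitalization.

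**Ceiling on events per parameter.** Formula: n × min(p, 1 − p)/k, largest at p = 0.5.
- n = 90, k = 6: 45/6 = 7.5
- n = 90, k = 9: 45/9 = 5.0
- n = 68, k = 6: 34/6 = 5.7
- n = 68, k = 9: 34/9 = 3.8

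The familiar guide of 10 would need 60 in the rarer category: 120 participants at a 50% rate, 300 at 20%. That guide is a rule of thumb, so the consequence was simulated.

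**Simulation.** Maximum likelihood, six terms, true odds ratio 0.5, modest assumed covariate effects, 2,000 runs per row. The rate is over both arms. Failed means separation or non-convergence. Inflation is the relative excess of the mean log odds ratio among fits that converged; its Monte Carlo error is about 2-3 percentage points at rates of 20-50% and 3-7 points below that.

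| Event rate | n = 90: events per parameter | Failed | Inflation | n = 68: events per parameter | Failed | Inflation |
|---|---|---|---|---|---|---|
| 5% | 0.75 | 54% | −19% | 0.6 | 69% | −12% |
| 10% | 1.5 | 19% | 18% | 1.1 | 33% | 5% |
| 20% | 3.0 | 4% | 18% | 2.3 | 7.5% | 21% |
| 30% | 4.5 | 0.7% | 12% | 3.4 | 2.2% | 15% |
| 40% | 6.0 | 0.2% | 11% | 4.5 | 0.9% | 16% |
| 50% | 7.5 | 0.3% | 9% | 5.7 | 1.5% | 12% |

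At 20% and n = 90 the mean log odds ratio is −0.821, so exp(−0.821) = 0.44 against 0.50; at 50% it is exp(−0.758) = 0.47. At 30-50% the bias is 0.06-0.11 on the log scale against a standard deviation of 0.49-0.70, and 95% intervals cover 94-95% of the time. With a true odds ratio of 1 (n = 68, rates 10-50%) the mean log odds ratio is −0.02 to 0.01 and the rejection rate 3-6%.

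**Rate defined in the control arm.** A 20% control rate with odds ratio 0.5 means odds of 0.25 × 0.5 = 0.125 in the other arm, or 11.1%. The overall rate is then 15.6%, about 14 events in 90. Runs on this footing, with other assumed covariates, gave failure of 7-9% at n = 90 and 14-15% at n = 67-68. Inflation over 20-50% control rates with six terms ran from 7% to about 20% (22% in the worst case). A 10% control rate is an overall 7.6%, between the first two rows of the table, which is where the upper figure of about 50% failure at the smaller sample belongs.

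**Nine terms (assumed quintiles).** At n = 90 failure is 13.5%, 0.4% and 0.3% at rates of 20%, 40% and 50%, with inflation of 14-19%. At n = 68 failure is 33% at a 20% rate and 1.8% at 50%, with inflation of 23-33% over rates of 10-50%.

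**Firth's penalized likelihood, same covariates.** One set of runs gave mean odds ratios of 0.48-0.50 at control rates of 20-50%, with at most 0.1% failures. Another gave almost no failures, bias within about 10%, and root mean squared error 10-14% below maximum likelihood.

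**The case against.** The strongest reply is that the ceiling of 7.5 follows from the sample size alone, but the harm does not. A reader might infer that these odds ratios will be biased away from 1, or the models will fail, at any event rate. The results above do not support that. With six terms, failures are rare at 30-50% and the bias is small against the standard error. At a 5% rate the surviving fits are pulled toward 1, and under no effect there is no bias and no excess of false positives. This part of the reply stands in full.

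Three further replies stand in part:
- The sample may remain close to 90, because the outcomes come from linked records and the 25% drop-out belongs to the primary-outcome calculation. The n = 68 figures are therefore the pessimistic end. The nine-term figures rest on an unstated coding.
- Adjusting for prognostic variables in a randomized trial is accepted practice. A reader might infer from the label of confounders that the adjustment is itself a mistake, or that the covariates should be removed. That does not follow. Randomization removes the need for confounding control but not the case for prognostic adjustment, and which variables to keep is a debatable trade-off, particularly as both stratification factors (center and IBD-DI severity) would have a claim.
- The analysis plan is not shown and may already specify how sparse data are handled. If it specifies a penalized fit, the point is met. What remains is that the protocol fixes the covariate set without exception for models this small.

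**Conclusion.** The concern holds in a limited form. The protocol commits two secondary logistic models to at least six parameters with no more than 7.5 events per parameter. Under ordinary maximum likelihood and a true odds ratio of 0.5, that means a log odds ratio about 7-20% too extreme at event rates of 20-50%. The risk of separation is negligible for common events (under 3% at about 35-50%), material at about 20% (4-15%) and serious at about 10% (19-50%). Hospitalization is the outcome more likely to be uncommon, but the document does not say so with a figure.

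These sizes depend on assumed event rates, covariate distributions and covariate effects. Only the ceiling is free of assumptions about event rates. The primary comparison is untouched. This is a minor point and a cheap improvement.

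**What to change.** In the health services paragraph of the Statistical analysis section, state that the logistic models for emergency department use and hospitalization will be fitted with Firth's penalized likelihood, with profile penalized-likelihood confidence intervals. Keep the named covariates, enter socioeconomic status as a single term, and report an arm-only risk difference next to each odds ratio.

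The change is to wording only and needs no new data. The cost is slightly less familiar software and slightly less direct comparability with odds ratios from earlier observational studies.

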**Fig. 1 Fig1:**
[figure not shown]
Patient flow

Inclusion criteria: We will enroll adolescents aged 16–17.5 years with IBD diagnosed > 6 months before recruitment using standard criteria [20]. Since most adolescents are transferred to adult care around 18 years of age, this would allow for at least one year of post-transfer follow-up due to the 3-year length of the grant funding. Study participants must have the ability to speak/read English at a functional (Grade 8) level, intention to reside in Canada after transfer to adult care, and ability to use a smartphone or personal computer for the virtual intervention components. In Canada, > 95% of adolescent IBD patients in Canada have access to technology to complete study requirements [21, 22].

Exclusion criteria: Adolescents who do not fluently speak English, those intending to leave Canada after graduation from high school, and those unwilling to be involved will be excluded. We will maintain a record of ineligible patients, and those who declined enrollment and the reasons for doing so, to inform the feasibility of post-RCT implementation in clinical practice.

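### The utilization models adjust for age at transfer, which is fixed after randomization, and the outcome window has two different starts and no single end

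*Protocol article*

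**What the plan says.** **Covariates.** For every utilization model, the Statistical analysis section prescribes adjustment for "age at diagnosis, age at transfer, sex, rural/urban household, and socioeconomic status". Age at transfer is thus fixed for all utilization models and is called a confounder.

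**Order of events.** Research staff "randomize them at enrollment (1:1", stratified by center and IBD-DI severity (Randomization section). The inclusion criteria read "We will enroll adolescents aged 16–17.5 years with IBD", and add that "most adolescents are transferred to adult care around 18 years of age".

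**Start of the window.** Table 5 defines the outcome as "Emergency department visit after 18th birthday (yes/no", and likewise counts hospitalization and visits from the 18th birthday. The analysis section says: "Likelihood of emergency department use and hospitalization after transfer will be compared using multivariable logistic regression analysis".

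**End of the window.** Table 5 collects these outcomes at T3, "at the end of the study period (1–2 years after transfer) (T3". Under Outcome measures, Aim 1, the primary outcome is instead placed 3 years after enrollment. Table 2 says that completion of the intervention depends on how ready the patient is and how well the skills exercises have gone, typically 1–2 years after transfer depending on age at enrollment.

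**The concern.** A variable that takes its value after randomization cannot confound a randomized comparison. It can be a consequence of treatment, and here the program's whole purpose is the transition process. If the program moves the date of transfer, and sicker patients also transfer earlier or later and use more care, then comparing arms at equal transfer age compares patients of unequal severity. That undoes part of what randomization provides. The covariate list comes from observational health services studies, where transfer age may be a reasonable adjustment. It does not name center or IBD-DI stratum, the two factors by which this trial randomizes.

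The window raises a second problem. A visit between the 18th birthday and transfer counts under one section and not under the other. With no single end, participants are observed for different lengths of time, and a logistic model of any event against none, as described, does not distinguish a short window from a long one. The Outcome measures section calls the utilization effect an important determination, and the Limitations section relies on utilization to judge cost-effectiveness. A reader will need to know what the odds ratio means.

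**Working it through.** The protocol gives no event rate and no computed figure for utilization, so there is nothing of its own to reproduce. Rates and shifts below are assumptions.

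**1. Is age at transfer a baseline variable?** Randomization is at age 16.0 to 17.5 and transfer around 18. The gap is 18 − 17.5 = 0.5 year to 18 − 16.0 = 2 years. Transfer age is not known at randomization.

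**2. How long is the window?**
- T3 rule: 1 to 2 years after transfer.
- Three years after enrollment: age 16.0 + 3 = 19.0 to 17.5 + 3 = 20.5, which is 1.0 to 2.5 years after the 18th birthday.

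**3. What does window length do to a yes/no outcome?** With a constant rate λ per year, P(any event) = 1 − exp(−λT).

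| λ (assumed) | T = 1 year | T = 2 years |
|---|---|---|
| 0.2 | 1 − exp(−0.2) = 18% | 1 − exp(−0.4) = 33% |
| 0.3 | 1 − exp(−0.3) = 26% | 1 − exp(−0.6) = 45% |

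These compare a participant at one end of the T3 range with one at the other. They do not compare arms.

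**4. What does the odds ratio mean?** The odds of any event are exp(λT) − 1. Take a control rate of 0.25 and a true rate ratio of 0.6, giving 0.15 in the intervention arm. At T = 1, OR = (exp(0.15) − 1)/(exp(0.25) − 1) = 0.57. At T = 2, OR = (exp(0.30) − 1)/(exp(0.50) − 1) = 0.54. The same effect yields a somewhat different odds ratio as the window changes.

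**5. When is there bias?** Logistic models were fitted to 400,000 simulated participants with no treatment effect. Severity U is standard normal. The event rate is 0.25·exp(0.6U) per year. Transfer age is 18 + 0.25U + a normal error with SD 0.25 + any arm shift. The window is uniform on 1 to 2 years, plus any arm shift.

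| Scenario | OR without transfer age | OR with transfer age |
|---|---|---|
| No arm effect on transfer or window | 0.99 | 0.99 |
| Window is 3 years from enrollment, counted from age 18 | 1.00 | 1.00 |
| Program delays transfer 0.25 year | 1.00 | 0.70 |
| Program delays transfer 0.5 year | 1.00 | 0.49 |
| Intervention window ends 0.25 year later | 1.20 | 1.21 |
| Intervention window ends 0.5 year later | 1.42 | 1.45 |

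Rows 3 and 4 show bias created by the adjustment. Rows 5 and 6 show bias from a window that differs by arm, which adjusting for transfer age does not remove. Rows 1 and 2 show that neither problem biases the comparison when the arm affects neither transfer timing nor the window.

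The start matters as well. If the window runs from transfer to 3 years after enrollment, a 0.25-year delay in transfer shortens the intervention window, and the OR is 0.81 without and 0.70 with the adjustment.

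**The case against.** The strongest reply is that every route to bias needs an assumption that the protocol does not make.

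- **Transfer timing.** Nothing says that the program changes when patients transfer. The navigators prepare and support them, and transfer is tied to age 18, which limits its spread. Without an arm effect on timing, the adjustment is harmless (row 1). This stands: a reader might infer that the planned estimates are biased, but the documents show only that they could be.
- **Unequal windows.** Differences that come from age at enrollment are set by a baseline variable and balanced by randomization. This also stands. They add noise and change the meaning of the odds ratio, but do not bias it.
- **Windows that differ by arm.** The sentence in Table 2 concerns completion of the intervention and does not define the utilization window. Table 5 gives one T3 rule for both arms, and the events come from linked administrative data rather than a visit. A reader might combine the 2.5-year upper limit with an arm-dependent end, but these come from different rules. An end 3 years after enrollment is the same in both arms.
- **Matters for the SAP.** Person-time handling, including an offset for the count models, may be specified there. A list of what all models include does not exclude center or stratum. Both are fair, so the absence of these terms is not in itself an error.

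The reply does not touch two statements in the text: a post-randomization covariate is required in every model, and the two sections start the window at different points.

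**Conclusion.** The point holds in limited form. The protocol requires adjustment for a variable fixed 0.5 to 2 years after randomization and wrongly treats it as a confounder. It also contradicts itself on when the utilization window starts and leaves two candidate ends. These are stated rules, so an unseen SAP would have to override them and not merely add detail.

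The consequence is conditional. Bias from age at transfer needs a program effect on timing together with another factor that affects both timing and utilization. Under the assumed delays of 0.25 and 0.5 year, the null odds ratio moves to 0.70 and 0.49; without a delay it does not move. Bias from the window needs its length to differ by arm, which would be possible if the end followed intervention completion. The contrasts of 26% against 45%, and 18% against 33%, illustrate how strongly follow-up length affects a yes/no outcome in individuals. They are not an estimate of a difference between arms.

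These are secondary outcomes. The primary IBD-DI comparison is unaffected. The change is worth making because it is cheap and removes the question.

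**What to change.** 1. Replace age at transfer with age at randomization in all utilization models.
2. Add center and baseline IBD-DI stratum to the named covariates.
3. Reconcile Table 5 with the Statistical analysis section on the start of the window.
4. Define the utilization outcomes over one fixed window, identical in both arms and independent of intervention completion, from the linked data. An example is the 12 months from the 18th birthday. It starts at a point that treatment cannot move and ends at age 19.0, which even a participant enrolled at 16.0 reaches within 3 years.
5. If variable follow-up is kept instead, use a log person-time offset for the counts and a time-to-first-event model for the yes/no outcomes.

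The cost is wording in the protocol and analysis plan. No new data are needed: the linkage to Ontario and British Columbia records is already planned, and the four named sites are in those provinces. The downside is that events outside the fixed window move to a secondary analysis. The article reports that recruitment had not begun at submission, so at that stage the change could precede any outcome data.
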